### Other outcomes

#### Physiotherapeutic assessments

The two physiotherapy assessments Y-Balance Test and One Leg Hop Test are used as objective criteria for the function of the knee joint in terms of lower limb strength and dynamic balance before the intervention, after 6, 12 and 24 months.^37 38^ Both assessments are widely used in clinical settings and have demonstrated good test–retest reliability in healthy individuals, with ICC values ranging from 0.85 to 0.88 for the Y-Balance Test^39^ and from 0.94 to 0.96 for the One-Leg Hop Test.^40^

The assessments are carried out by the treating therapists, who have previously received online training and written instructions.

#### Activity tracker

During the study, Xiaomi Smart Band 8 activity trackers (Xiaomi, Haidian, Beijing, China) will be worn by patients for 1 week prior to each assessment time point (baseline, 6, 12 and 24 months) to determine their activity level and assess a potential correlation between physical activity and clinical outcomes (eg, pain levels in more vs less active patients). The activity trackers will record the total number of steps taken over each 1 week period as well as the average number of steps per day. This correlation may help in the interpretation of clinical outcomes.

#### Health economic outcomes

The condition-related costs over a 24-month period will be assessed from the perspective of a healthcare payer as well as from a societal perspective, including the costs associated with lost productivity. Quality-adjusted life years will be calculated over the 24-month period. The incremental cost-effectiveness at 24 months will be expressed as the cost per quality-adjusted life year gained, from both the healthcare payer and societal perspectives.

On a self-designed questionnaire, patients will report healthcare utilisation (medical resource use) and professional activity (productivity) at baseline (covering 6 months retrospectively) and at each follow-up time point (covering the time since the previous follow-up). Medical resource use and costs accrued at the treating medical centre will additionally be collected on the basis of administrative/financial data, from a subset of centres.

### Participant timeline {13}

Table 1 provides an overview of the participant timeline, from the first visit to the last follow-up measurement, including all assessments that are conducted.

**Table 1 T1:** Participant timeline

Study periods	Screening	Treatment			Follow-up			
		N-TEC		Control (PRP)				
Visit	1	2a	2b	2	3	4	5	6
Time (hour, day, week, month)	≤ 6 m	Day −32	Day 0	Day 0, 7,14	6w	6m	12m	24m
Day	≤ 180	- 32	0	0, 7, 14	42	180	360	720
Acceptable time delay		0d	1d	2d	2w	4w	6w	8w
PIC	x							
Medical history	x							
Inclusion/exclusion criteria	x							
Laboratory tests (serology)	x	x						
Pregnancy test	x							
MRI*	x	(x)				x	x	x
X-ray*	x	(x)				x	x	x
Questionnaires†	x	(x)				x	x	x
EQ-5D-5L	x	(x)	x		x	x	x	x
Health economic data	x				x	x	x	x
Physiotherapy tests	x					x	x	x
Harvesting of nasal cartilage biopsy		x						
Surgery (implantation)			x					
PRP injection				x				
Clinical examination	x	x	x	x	x	x	x	x
Adverse events‡	x	x	x	x	x	x	x	x
Physiotherapy§			x	x	x	x		

* MRI and X-ray must be repeated if they were not performed during screening or were conducted more than 6 months before treatment (day 0).

† Questionnaires must be repeated if completed more than 1 month prior to treatment (day 0).

‡ Recording of the adverse events is a permanent process independent of specific visit.

§ Physiotherapy sessions will be performed continuously as prescribed by surgeon independent of specific visit. Physiotherapy is performed for 18 weeks (4.5 months) but can be prolonged if medically indicated.

EQ-5D-5L, European Quality of Life-5 Dimensions; N-TEC, nasal chondrocyte tissue-engineered cartilage; PIC, patient informed consent; PRP, platelet-rich plasma.

### Sample size {14}

The sample size was estimated assuming that the data will be analysed in a linear model with treatment as the variable of interest and KOOS at baseline as a covariate. It is assumed that patients will be randomised 1:1 (N-TEC:PRP). Based on published data, we assumed that the SD of the KOOS is 17.2 (pooled SD in both arms at baseline, number of patients: 183).^41^ Furthermore, we assumed that patients treated with PRP gain 10 points, whereas patients with N-TEC improve 25 KOOS pain units from baseline to 24 months. Recruiting a total of 75 patients allows to estimate a difference in the change in KOOS between the intervention arm and the control arm of 15 points with a power of over 90% and a two-sided alpha of 5%, assuming a dropout rate of 20% (15 patients).

### Recruitment {15}

Patients attending for normal consultation at the nine clinical centres will be screened for participation. If diagnosed with PFOA grade 1–3 according to Iwano classification patients will be informed of the trial and asked to participate. There is no advertisement for recruitment since no healthy volunteers are eligible for the trial. No compensation or payment will be given to the participants.

### Sequence generation {16a}

Patients will be randomly assigned either to injection of PRP or N-TEC implantation. The randomisation procedure will be implemented by the Clinical Data Centre of the Department of Clinical Research of the University Hospital Basel into the Clinical Data Management System (CDMS) REDCap^®^ per list. Randomisation will be stratified by study centre, with patients having a 50% probability to be randomised to the specific arm. In case the within centre imbalance between study arms will be equal to or larger than three, a ‘biased coin’ will be implemented such that patients will have an 80% probability to be allocated to the group that would minimise the imbalance between arms. This will reduce the imbalance within centre while ensuring allocation concealment to prevent selection bias in this open label study.

### Concealment mechanism {16b}

The assignment is not secret and is communicated to the person taking part, the doctor and the persons providing follow-up treatment.

### Implementation {16c}

Participants will be screened and enrolled by the respective principal investigator during their usual medical consultation in nine different centres (six in Switzerland, two in Germany, one in Croatia). Allocation to treatment groups is computerised.

## Assignment of interventions: blinding

### Who will be blinded {17a}

The study is not blinded as blinding of patients is not possible for ethical reasons (injection vs surgery). Also, assessors of MRI/X-ray cannot be blinded, as an experienced person will detect the implantation of the graft.

### Procedure for unblinding if needed {17b}

Not applicable, because the design is open label.

## Data collection and management

### Plans for assessment and collection of outcomes {18a}

Study data will be captured via the online CDMS REDCap^®^, based at the IT Department of the University Hospital Basel. The questionnaire as a measure for the patient- reported outcomes will be included in the electronic CRF to be filled in by the patient before the visit or directly at the site online or on paper.

All investigators directly involved in the patients’ information about the study, study intervention and follow-up will have to provide the certificate of Good Clinical Practice (GCP) training and/or follow additional national and local requirements on investigator qualification.

All outcomes are evaluated at baseline, and at 6-month, 12-month and 24-month follow-ups. Furthermore, the EQ-5D-5L and health economic data will be collected at the clinical visit scheduled for 6 weeks post-intervention.

### Plans to promote participant retention and complete follow-up {18b}

Data will be collected until the time of withdrawal using the questionnaires and MRIs at the time of follow-up. No data will be collected afterwards. A final medical visit is recommended for the safety of the patient after withdrawal (minimum 1 year after treatment).

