### Criteria for discontinuing or modifying allocated interventions {11b}

Patients can be excluded from the study by the respective PIs at any point for the following reasons:

Medical reasons where a continuation of the trial would jeopardise the health of the patient.Withdrawal of informed consent (final medical follow-up mandatory for patient safety).Non-compliance with the required procedures as stated in the patient information and informed consent or refusal of the follow-up examinations, which are necessary to assess the safety and efficacy of the treatment.Abortion of the clinical study.Contamination of the IMP during manufacturing.IMP manufacturing not successful.

For the experimental surgical approach, dose modifications are not possible. For the control group, no dose modifications are planned.

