## Statistical methods

### Statistical methods for primary and secondary outcomes {20a}

The primary analysis will be based on the per-protocol estimand. Follow-up (change from baseline to 24 months) KOOS Pain values will be compared between the treatment arms using a linear regression model including baseline values as covariate (analysis of covariance (ANCOVA)) and centre as fixed effect. The model-based estimate of the treatment effect of tissue implantation as compared with plasma injection together with its 95% CI and p value will be presented. At the moment, the number of patients with a recurrent event is not assessable. Depending on this number and the distribution between the treatment arms, the per-protocol estimand may not be conservative. Therefore, the main estimand will be presented with the intention-to-treat estimand, and the number of intercurrent events will be listed by treatment arm. Possible bias due to intercurrent events will be discussed together with the results.

For demographic baseline variables, summary statistics will be presented. Continuous variables will be summarised by mean and SD in case of an assumed normal distribution or by median and IQR otherwise. Binary and categorical variables will be summarised by frequencies and percentages. KOOS Pain scores at 6 and 12 months as well as further KOOS subscales will be analysed in a similar fashion as the primary outcome namely based on ANCOVA, with the outcome as the dependent variable, the treatment arm as predictor and the baseline outcome value as covariate. The estimated, baseline-adjusted treatment effect of tissue implantation as compared with plasma injection will be reported together with its 95% CI. In case there are centres with fewer than five patients, these will be pooled with the next largest centre. Furthermore, summary statistics will be presented for the values at each assessed timepoint according to treatment arm, with outcomes summarised by mean and SD in case of an assumed normal distribution and by median and IQR otherwise. We will display the time course of the outcomes by appropriate graphics. Treatment failures will be summarised by frequencies and percentages. The proportion of patients with deterioration and non-response will be shown according to Iwano class.

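### Patients excluded for failed manufacture or non-compliance would have no observed 24-month KOOS Pain, so the promised intention-to-treat estimate would have to drop or impute them

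*Protocol article*

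**What the plan says.** Section {11b} is headed as criteria for discontinuing or modifying the allocated intervention, but its list concerns leaving the trial: "Patients can be excluded from the study by the respective PIs at any point for the following reasons". Among the reasons are "Non-compliance with the required procedures as stated in the patient information and informed consent or refusal of the follow-up examinations" and two manufacturing items that run together in the text, "Contamination of the IMP during manufacturing.IMP manufacturing not successful".

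Section {18b}, on retention, says: "Data will be collected until the time of withdrawal using the questionnaires and MRIs at the time of follow-up". It continues: "No data will be collected afterwards".

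Section {20a} makes the per-protocol estimand primary, concedes that it may not be conservative, depending on how many intercurrent events occur and in which arm, and therefore states that "the main estimand will be presented with the intention-to-treat estimand". Intercurrent events are to be listed by arm and the possible bias discussed.

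Section {20c} has one missing-data rule for death and one for loss to follow-up (missing at random, with multiple imputation to be considered). It has none for patients whom an investigator excludes.

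On the closing visit, section {11b} attaches to consent withdrawal the words "final medical follow-up mandatory for patient safety", whereas section {18b} reads "A final medical visit is recommended for the safety of the patient after withdrawal (minimum 1 year after treatment".

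**The concern.** An intention-to-treat estimate differs from a per-protocol one through the patients who did not receive or complete what they were assigned. Section {20a} brings it in because those patients may make the per-protocol result flattering. If the same patients leave the study and are no longer measured, the comparison loses the observations that would show the difference.

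Part of the loss is also one-sided. A failed or contaminated graft can occur only in the N-TEC arm. It occurs after assignment: section {26a} assigns patients once eligibility is confirmed, and Table 1 places the nasal biopsy at day −32, with about four weeks of manufacture to follow. An analysis plan can choose how to handle missing values, but it cannot recover outcomes that the protocol did not collect.

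**Working it through.** **The plan's own figure.** Section {14} assumes SD 17.2, gains of 10 (PRP) and 25 (N-TEC), two-sided alpha 5%, and 75 patients less 15 dropouts, so 60 analysed, 30 per arm. Power for a 15-point difference is 92.2% by the normal approximation and 91.3% by the noncentral t. The stated figure of over 90% reproduces and is not in dispute.

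**Tracing one patient.** Take a patient assigned to N-TEC whose graft fails.

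1. Section {11b} permits exclusion from the study on that ground.
2. If the stopping rule in section {18b} covers this exit, no 6-, 12- or 24-month questionnaire is collected.
3. Table 1 counts follow-up from treatment day 0, which this patient never reaches, and no text says what date replaces it.
4. Section {20a} still needs this patient's 24-month change for the intention-to-treat estimate.
5. Section {20c} does not say what is done when that value is absent because of an exclusion.

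The estimate must then either omit the patient or impute a value.

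**Size.** The article gives neither a manufacturing failure rate nor an outcome for unimplanted patients, so the following are assumptions:

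- N-TEC arm: 37 patients (75/2 = 37.5, rounded down).
- Number never implanted: m = 2 or 4.
- Their true gain: g = 0 to 10 points, where 10 is the plan's PRP gain.
- Implanted patients gain 25 on average, as planned, and imputed values centre on 25.

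Overstatement = (m/37) × (25 − g).

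| m | g = 10 | g = 0 |
|---|---|---|
| 2 | 2/37 × 15 = 0.81 | 2/37 × 25 = 1.35 |
| 4 | 4/37 × 15 = 1.62 | 4/37 × 25 = 2.70 |

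The intention-to-treat difference with everyone observed would be 15 − 0.81 = 14.19 at one end and 15 − 2.70 = 12.30 at the other. The reported one would stay near 15. Omitting the patients gives the same gap, because the N-TEC mean is again that of implanted patients. The largest value is 2.70/15 = 18% of the target.

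**Scale.** With 37.5 per arm the standard error of the difference is 17.2 × √(2/37.5) ≈ 3.97, so the overstatement is about 0.2 to 0.7 standard errors.

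**Wider range.** If 20% of the arm were never implanted, the gap would be 0.20 × 15 = 3.0 to 0.20 × 25 = 5.0 points. Nothing in the article supports a rate that high; it only shows how the result scales.

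**The case against.** Much can be said for the plan, and most of it limits the point without removing it.

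- **Exclusion is permissive.** Section {11b} says patients can be excluded, so a reader who infers that every failed graft ends follow-up goes too far. The gap concerns those actually excluded.
- **Withdrawal may mean withdrawal of consent only.** On that reading the stopping rule in section {18b} is unremarkable. But follow-up of excluded patients is then undefined, and the same clarification is needed.
- **The bias mechanism is not written down.** One might infer that the plan fills these values from implanted patients. Section {20c} says only that imputation will be considered, and only for loss to follow-up. The overstatement is therefore conditional.
- **The intention-to-treat estimate is not empty.** Patients who switch to another regenerative operation or to knee replacement count as treatment failures and are not on the exclusion list, so it can still inform on them. Listing intercurrent events by arm would also make one-sided losses visible, though not their outcomes.
- **Some losses are unavoidable.** Patients who withdraw consent or refuse follow-up cannot be measured under any wording.
- **The dropout allowance is not used up.** Two to four patients are a small part of the 15 allowed.
- **An untreated patient is not wholly without a date.** For anyone biopsied at day −32, a planned day 0 can be worked out. The text does not say to use it.
- **This is a condensed article.** The full protocol may say more, but the rules printed here, if followed, lose the data.

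**Conclusion.** The point holds in a limited form. As printed, sections {11b} and {18b} allow patients with failed or contaminated manufacture, or with non-compliance, to leave the study and go unmeasured, and no section keeps them in follow-up. For those patients the intention-to-treat estimate, offered as the counterweight to a possibly non-conservative per-protocol result, has no observed 24-month KOOS Pain.

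The likely size is modest: about 0.8 to 2.7 points on a 15-point target. That rests on the assumed 2 to 4 unimplanted patients of 37, on gains of 0 to 10 points, and on their being omitted or imputed from implanted patients.

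A reader might infer that the primary result or the sample size is wrong. The article does not support this: the primary analysis is per-protocol and the stated power reproduces.

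Separately, the final medical visit is called mandatory in one section and recommended in the other. The two must be reconciled.

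**What to change.** In sections {11b} and {18b}, separate stopping the allocated intervention from leaving the study:

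- Restate manufacturing failure, contamination and non-compliance with study procedures as reasons why the allocated intervention was not given or completed, not as reasons for study exclusion. They need not be deleted.
- Limit the end of data collection to withdrawal of consent.
- Continue the online questionnaires and adverse-event reporting at 6, 12 and 24 months for every randomised patient who has not withdrawn consent. For untreated patients, time these from the planned day 0 or from randomisation, and say which.
- State that these observed values enter the intention-to-treat estimate.
- Reconcile the wording on the final medical visit across the two sections.

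The cost is a protocol wording change and a few extra questionnaires for a handful of patients, since KOOS is already completed online. Recruitment began on 6 June 2024, and outcomes missed in the meantime cannot be recovered later, so the change is worth making early.

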### Data management {19}

Study data will be captured via the online CDMS REDCap^®^, based at the IT Department of the University Hospital Basel. The data collected is entered into the study eCRF. An audit trail will maintain a record of initial entries and any changes made; time and date of entry and username of person authorising entry or change. For each patient enrolled an eCRF must be completed. The principal investigator and coinvestigator at the study site will be responsible for assuring that the data entered into the eCRF are complete, accurate and that the entry and updates are performed in timely manner. If a patient withdraws from the study, the reason must be noted on a dropout form of the eCRF.

### Confidentiality {27}

Data will be collected only from patients who have given their written consent to our study. Their medical records will be handled confidentially. Only members of the study team, monitors and the respective authorities (competent authorities) will have access to the data. An enrolment log will be kept at each site as well as a code list to link the patient’s name with their patient ID. Documents will be stored according to the hospital regulations, but for a minimum of 30 years.

### Plans for collection, laboratory evaluation and storage of biological specimens for genetic or molecular analysis in this trial/future use {33}

Consent of the patient has to be obtained for the use of excessive cells for research purposes. Excessive cells not used for the generation of the implant will be stored in the research laboratories in Basel and Würzburg and used for research to deepen knowledge in the diseases. All biological materials given to the lab will be encoded. Only the principal investigators have access to the code. No connection is made between the biological material and patient data.

## Statistical methods

### Statistical methods for primary and secondary outcomes {20a}

The primary analysis will be based on the per-protocol estimand. Follow-up (change from baseline to 24 months) KOOS Pain values will be compared between the treatment arms using a linear regression model including baseline values as covariate (analysis of covariance (ANCOVA)) and centre as fixed effect. The model-based estimate of the treatment effect of tissue implantation as compared with plasma injection together with its 95% CI and p value will be presented. At the moment, the number of patients with a recurrent event is not assessable. Depending on this number and the distribution between the treatment arms, the per-protocol estimand may not be conservative. Therefore, the main estimand will be presented with the intention-to-treat estimand, and the number of intercurrent events will be listed by treatment arm. Possible bias due to intercurrent events will be discussed together with the results.

For demographic baseline variables, summary statistics will be presented. Continuous variables will be summarised by mean and SD in case of an assumed normal distribution or by median and IQR otherwise. Binary and categorical variables will be summarised by frequencies and percentages. KOOS Pain scores at 6 and 12 months as well as further KOOS subscales will be analysed in a similar fashion as the primary outcome namely based on ANCOVA, with the outcome as the dependent variable, the treatment arm as predictor and the baseline outcome value as covariate. The estimated, baseline-adjusted treatment effect of tissue implantation as compared with plasma injection will be reported together with its 95% CI. In case there are centres with fewer than five patients, these will be pooled with the next largest centre. Furthermore, summary statistics will be presented for the values at each assessed timepoint according to treatment arm, with outcomes summarised by mean and SD in case of an assumed normal distribution and by median and IQR otherwise. We will display the time course of the outcomes by appropriate graphics. Treatment failures will be summarised by frequencies and percentages. The proportion of patients with deterioration and non-response will be shown according to Iwano class.

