### Trial design {8}

This study is a randomised, open, controlled, parallel-group, prospective superiority trial (phase II) to evaluate the efficacy of implantation of N-TEC versus injection of PRP for the treatment of PFOA. A total of 75 patients, suffering from symptomatic PFOA (Iwano grade 1–3) will be randomised one to one to either N-TEC or to the active comparator control group (Injection of PRP). The experimental group will receive the implant, while the control group will undergo three intra-articular injections over a 3-week period. Both groups will subsequently participate in an 18-week physiotherapy programme and will be followed up for 2 years.

The adapted Consolidated Standards of Reporting Trials (CONSORT) 2010 study design flow diagram provides an overview of the study procedures, including key phases such as participant recruitment, treatment and follow-up assessments (figure 1).^19^

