##### Treatment failures

Treatment failure is defined as objective pathological clinical findings by the investigator directly correlated with subjective patients’ complaints resulting in a clinical deterioration of the subjective clinical outcome assessed by KOOS. Moreover, a patient is considered as treatment failure, when switching to an alternative surgical regenerative treatment or knee replacement. A clinical deterioration is defined as reduction in the KOOS score of >13 compared with baseline.

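### The primary p value of this open-label superiority trial rests on a per-protocol estimand, and the intention-to-treat result has no decision role

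*Protocol article*

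**What the plan says.** All references are to the protocol article.

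- **Statistical methods {20a}.** "The primary analysis will be based on the per-protocol estimand". The ANCOVA estimate, its 95% CI and the p value are described directly after this. The section says that the number of events cannot be foreseen and that, depending on their number and distribution, "the per-protocol estimand may not be conservative". Its answer is that "the main estimand will be presented with the intention-to-treat estimand", with intercurrent events listed by arm and possible bias discussed. It does not say which result governs if the two disagree.
- **Objectives {7} and Trial design {8}.** The aim is superiority in KOOS Pain change at 24 months, in an open, 1:1 randomised phase II trial.
- **Criteria for discontinuing {11b}.** Site principal investigators can exclude patients from the study at any point. The grounds include "Medical reasons where a continuation of the trial would jeopardise the health of the patient", non-compliance or refusal of follow-up, contaminated product, and "IMP manufacturing not successful".
- **Informed consent {26a} and Intervention description {11a}.** Assignment follows the eligibility check. In the N-TEC arm, four weeks then pass between nasal biopsy and implantation.
- **Treatment failures.** A patient also counts as a failure "when switching to an alternative surgical regenerative treatment or knee replacement". The article does not say how such a patient enters the primary analysis.
- **Retention {18b} and Missing data {20c}.** Data collection ends at withdrawal. For loss to follow-up, multiple imputation under missing at random will be considered.

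**The concern.** Randomisation protects a comparison of everyone randomised, as randomised. A per-protocol comparison keeps that protection only if leaving the analysis set is unrelated to outcome, or related in the same way in both arms. Here neither can be assumed. Patients and imaging assessors know the allocation, the endpoint is self-reported, and the article itself lists patients' expectation of greater benefit from surgery as a limitation. Two exclusion grounds exist only in the N-TEC arm, and several others could depend on how the patient is doing.

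At stake is the interpretation of the main result. If per-protocol is significant and ITT is not, the plan as written still attaches its primary p value to per-protocol and leaves the discrepancy to discussion after the data are known.

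**Working it through.** **1. The plan's own figure.** Inputs from Sample size {14}: difference 15 points (25 minus 10), SD 17.2, two-sided alpha 5%, 75 recruited, 20% dropout (15), so 60 evaluable and 30 per arm.

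- Standard error = 17.2 × √(2/30) = 4.44.
- 15 / 4.44 = 3.38.
- Power = Φ(3.38 − 1.96) = 92.2%; with the noncentral t, 91.3%.

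The stated power of over 90% is reproduced. The sample-size arithmetic is not at fault.

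**2. What exclusions do when there is no true effect.** The document gives no exclusion rate and no mechanism, so these are assumed scenarios. Simulation: 30 per arm, SD 17.2, two-sample t test, 100,000 runs. Differences are N-TEC minus PRP.

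| Patients removed | Bias (points) | Two-sided type I error | False wins for N-TEC (nominal 2.5%) |
|---|---|---|---|
| None | 0.0 | 5.0% | 2.5% |
| 3 N-TEC, at random | 0.0 | 5.0% | 2.5% |
| Worst 3 N-TEC | +3.2 | 12.7% | 12.1% |
| Worst 3 PRP | −3.2 | 12.6% | 0.6% |
| Worst 3 in each arm | 0.0 | 8.2% | 4.1% |

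Removing exactly the worst patients is an extreme case. A milder mechanism was run with baseline-adjusted ANCOVA, 37 against 38 patients, an assumed baseline correlation of 0.5 and 10,000 runs. Removing 2, 4 or 7 N-TEC patients at random from the worse half gave type I error of 5.0%, 6.2% and 9.4%, with bias of +0.6, +1.3 and +2.5 points.

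So exclusion from one arm alone does no harm to alpha. Exclusion from one arm that is related to outcome does, and its sign depends on which arm loses the patients.

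**3. What ITT could cost in power.** Assume that a fraction f of N-TEC patients do not benefit from the implant and gain 10 points, as assumed for PRP.

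- Difference = 15 − f × 15.
- SD averaged over arms = √(17.2² + f(1 − f) × 15² / 2).
- Power = Φ(difference / (SD × √(2/30)) − 1.96).

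| f | Difference | SD | Power, 30 per arm |
|---|---|---|---|
| 5% | 14.25 | 17.35 | 88.9% |
| 10% | 13.5 | 17.49 | 84.8% |
| 20% | 12.0 | 17.72 | 74.6% |

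At f = 20%, keeping the SD at 17.2 and using the noncentral t gives 75.7%, hence a range of about 75-76%. If those patients gained nothing at all, the normal formula gives 76.7% at 10% and 54.9% at 20%.

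**The case against.** The strongest case for the plan has four parts.

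- **The risk is disclosed.** ITT will be reported, events will be listed by arm, and a reader will see any discrepancy. This stands as mitigation, but it does not say which result decides.
- **The link to outcome is inference.** The article does not define the per-protocol set. The grounds in {11b} are for leaving the study, and treatment failure is a secondary outcome. A reader might infer that failures and switchers are dropped from the primary analysis; the document does not say so. This stands.
- **The grounds that are certainly arm-specific may be harmless.** Contamination and failed manufacture have no stated connection with 24-month pain, and random one-arm exclusion leaves alpha at 5%. A reader might infer that arm-specific exclusion by itself inflates the error; it does not.
- **Direction is open.** If PRP patients who do badly leave to obtain surgery, the bias works against N-TEC and false wins for it fall to about 0.6%. A reader might infer that per-protocol must favour N-TEC; that is not established.

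A reader might also infer that per-protocol exclusions quickly exhaust the power, with room for only about two beyond the 15 dropouts. The document does not support this. Exclusions under {11b} may already be counted among the 15, and baseline adjustment would add power. With an assumed baseline correlation of 0.3, power is still 91.9% at 56 evaluable patients.

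The phase II label does not remove the point, because the plan states a superiority aim with a two-sided 5% alpha.

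**Conclusion.** The point holds as a weakness in the choice of primary estimand. The p value for superiority sits on the analysis that the article itself says may not be conservative, and ITT, although planned, decides nothing. The direction and size of any bias cannot be derived from the document. A shift of about 3 points either way, with two-sided type I error of 12-13%, applies only if exactly the worst 3 of 30 leave one arm; milder mechanisms give 5% to 9%, and exclusion unrelated to outcome gives no inflation. These figures show what is possible and do not forecast the result. The case for change is that the direction and size cannot be known in advance, while the remedy is specific and inexpensive.

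**What to change.** 1. In Statistical methods {20a}, make the ITT estimand (all randomised patients, analysed as randomised) primary. State that the superiority conclusion is drawn from it, and keep per-protocol as supportive.
2. Reconcile Criteria for discontinuing {11b} with Retention {18b}, so that patients who do not receive or who discontinue the allocated treatment remain in outcome follow-up where consent allows. Without this, ITT would depend on imputation for just those patients.
3. Use the multiple imputation of {20c} for 24-month values that are still missing after loss to follow-up.

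**Cost.** The ITT analysis is already planned, so the statistical work is small, but the change goes beyond wording: follow-up questionnaires are needed for patients who would otherwise leave. The effect may be diluted. At 30 per arm, power is about 85% if 10% of N-TEC patients gain only 10 points, and about 75-76% if 20% do. The sponsor should check power on this basis. Recruitment began in June 2024, so the change should be made before outcome data are analysed.
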